**Methods:**

Three schools will participate. Within each school, three different groups will be formed from Year 7 and 8 classes: 1) Co-Designers; 2) HIIT Only; and 3) Control. The study will include two phases. In phase one, Group 1 will co-design HIIT workouts as part of the HPE curriculum using an iterative process with the researcher, teacher, and students as collaborators. This process will be evaluated using student discussions, student surveys, and teacher interviews. In phase two, Groups 1 and 2 will use the co-designed 10-minute HIIT workouts in HPE for 8-weeks. Group 3 (control) will continue their regular HPE lessons. All students will participate in cardiorespiratory fitness, muscular fitness, and executive function assessments before and after the HIIT program or control period. Students will complete questionnaires on their motivation, enjoyment, and self-efficacy of the workouts. Differences between groups will be assessed using linear regressions to account for covariates. Heart rate and rating of perceived exertion will be collected during each HIIT session. The implementation will be evaluated using the Framework for Effective Implementation. Ethical approval was granted by the University of Queensland Human Research Ethics Committee and other relevant bodies.

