#### Anthropometry

Students will be asked to remove shoes, hats, and any heavy or bulky clothing. Stature will be measured using a stadiometer. Students will be asked to stand with their feet together and have their heels against the back of the stadiometer while keeping their knees straight. They will be instructed to breathe in and stand tall. Their stature will be recorded to the nearest 0.01 m. Body mass will be measured using a calibrated scale. Students will be asked to stand on the scale facing forward with their arms by their side. Their body weight will be recorded to the nearest 0.1 kg. Body mass index (BMI) will be calculated as (body mass (kg) divided by stature (m) squared). To determine students’ weight categories, age and sex specific BMI cut points will be used [30]. Based on discussions with key stakeholders (school gatekeepers and teachers), these measures will only be collected at the baseline visit and will be used as covariates in the study to understand differences based on body weight status.

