#### General physical activity levels

Baseline general physical activity level data will be collected using the physical activity questionnaire for children (PAQ-C), a self-administered, 7-day recall instrument that generates a physical activity score based on eight items scored on a 5-point scale [31]. The questionnaire is reliable (ICC = 0.96) [32], and its convergent validity is supported through relationships with an activity rating question, a teacher’s rating of physical activity, and moderate to vigorous physical activity assessed by a separate inventory (*r* = 0.45 to *r* = 0.63) [33, 34]. Further, the PAQ-C is quick to complete (approximately 5 minutes), [35] and is one of three physical activity measures that received majority support within an expert group [34]. This questionnaire will only be completed prior to the intervention to understand participants baseline general physical activity levels, which will be used as a covariate in data analysis.

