### Data analysis

Data entry will be completed by one researcher with at least 10% checked by a second researcher. All data will be checked prior to analysis using range to assess any outliers or errors in data entry. To describe the population, descriptive statistics will be reported for each school separately. To determine the effect of the HIIT intervention on cardiorespiratory fitness, muscular fitness, and executive function, general linear models will be used to assess changes in the dependent variables with group (HIIT or control), timepoint, and group x time interaction included as independent variables. To determine the effect of involvement in co-design on students’ motivation, enjoyment, self-efficacy, feelings, and basic psychological needs, generalised linear models will be used to assess changes in the dependent variable, with group (Co-Design or not), timepoint, and group x time interaction included as dependent variables. Potential covariates, such as sex, age, BMI, involvement in co-design, baseline physical activity levels, baseline physical activity enjoyment, and baseline levels of the dependent variable will be identified using two-by-two tests and included in the model where appropriate.

The implementation of *Making a HIIT* will be evaluated using the Framework for Effective Implementation [20] across 8 components: 1) program reach – number of consenting schools and students; 2) dosage – number of HIIT workouts delivered and completed; 3) fidelity – students’ heart rate and RPE during HIIT workouts; 4) quality – variation in heart rate between students; 5) monitoring of control group – via heart rate; 6) responsiveness – student enjoyment and teacher perspectives; 7) adaption – modifications of the HIIT workouts by teachers; 8) differentiation – uniqueness of study.

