## Discussion

This paper presents the protocol for the *Making a HIIT* study. *Making a HIIT* will include the novel component of co-designing HIIT workouts with students and teachers within the HPE curriculum. Further, it will examine if co-designing HIIT workouts affects student engagement during the workouts and if it moderates any outcome variables. *Making a HIIT* will include three different school types (co-educational school, boys’ school, and girls’ school) to provide insight into the integration of this type of work within a variety of schools and HPE units to support the HPE curriculum and to investigate potential gender differences. Currently, there are limited process evaluations on HIIT interventions in schools [6]. *Making a HIIT* will aim to comprehensively evaluate the extent to which the intervention was completed as intended. This is pertinent to understanding the link between implementation and outcomes, especially given evidence supporting that high-intensity exercise could be driving health benefits. This study does not include randomisation as it is not feasible in our protocol based on school timetables and preferences for class involvement. However, quasi-experimental designs are widely used in school-based research and are useful for comparing groups and measuring change when randomisation is not possible [69]. Overall, the results of this study will provide useful insights into the meaningful implementation of school-based HIIT interventions that support both educative and health outcomes.

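### Covariates that are constant within a student, entered as main effects in a two-timepoint group x time model, do not adjust the effect estimate for confounding of change

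*Protocol article*

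**What the plan says.** For the fitness and executive-function outcomes, the phase two Data analysis section states that "general linear models will be used to assess changes in the dependent variables with group (HIIT or control), timepoint, and group x time interaction" will be the model terms. For the psychological outcomes, "generalised linear models will be used to assess changes in the dependent variable, with group (Co-Design or not), timepoint, and group x time interaction". A timepoint term implies two outcome rows per student, so the effect of interest is the interaction.

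The same section then names the candidates for adjustment, "Potential covariates, such as sex, age, BMI, involvement in co-design, baseline physical activity levels, baseline physical activity enjoyment, and baseline levels of the dependent variable", and says that they "will be identified using two-by-two tests and included in the model where appropriate". An interaction is spelled out for group with time. None is named for any covariate.

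Other sections confirm that the measured covariates are recorded once. On stature, mass and BMI, Anthropometry says that "these measures will only be collected at the baseline visit and will be used as covariates in the study". On the physical activity score, General physical activity levels says "This questionnaire will only be completed prior to the intervention". The Enjoyment section places the general-activity PACES before the intervention. Sex, co-design involvement and the baseline outcome are fixed for a student by nature, and age is listed as a single value.

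The abstract summarises the analysis as "Differences between groups will be assessed using linear regressions to account for covariates". The Discussion states "This study does not include randomisation as it is not feasible in our protocol".

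**The concern.** In a non-randomised comparison of classes, a reader expects listed covariates to protect the effect estimate. Here the effect is a within-student contrast (post minus pre, compared between groups), while each covariate, as a main effect, explains only differences between students. The two do not meet. The results paper could then report an adjusted effect that is the unadjusted one under another name.

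At stake is confounding of change. If the HIIT and control classes differ in age, sex mix or BMI, and these predict how much a student changes over a term, that difference stays in the estimate. So does regression to the mean when the groups start at different levels.

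The baseline outcome adds a second difficulty. On each pre-test row the covariate equals the outcome, so the residual variance of a stacked fit no longer has a clear meaning, and the standard error moves without any change in what is estimated.

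**Working it through.** The protocol gives no figure on this point to reproduce, so the check is algebra followed by simulation.

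**Algebra.** Code time as t = -1/2 (pre) and +1/2 (post). For student i, let g be group and x any covariate with one value per student.
- Over a student's two rows, the product of x with time sums to x(-1/2 + 1/2) = 0, and the product of x with group x time sums to xg(-1/2 + 1/2) = 0.
- With complete pairs the design therefore splits into two orthogonal blocks: {1, g, x} between students and {t, gt} within students.
- The coefficient of gt is thus mean change in one group minus mean change in the other, whatever x is added. Coding time 0/1 does not alter it. A random student intercept preserves the split.
- Adding x times t puts x into the within-student block. The coefficient of gt is then that of g when change is regressed on g and x.
- If the baseline outcome is also entered with its time interaction, the result equals post-test ANCOVA, because post = change + baseline.

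**Simulation.** Size from the protocol: 3 x 44 = 132 students, 44 control and 88 HIIT. The remaining settings are assumptions: true effect 0; groups differing in sex mix, age, BMI and physical activity; change depending on sex and on baseline level. One data set, 20 m shuttle run in laps:

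| Model | Group x time | SE |
|---|---|---|
| Stacked least squares, no covariates | 2.638 | 5.30 |
| + sex, age, BMI, physical activity | 2.638 | 5.00 |
| + co-design and baseline outcome | 2.638 | 2.02 |
| Random-intercept model, without or with the four covariates | 2.638 | 2.07 |
| GEE, without or with all six covariates | 2.638 | 2.14 |
| Four covariates, each with its time interaction | 0.753 | not recorded |
| Change regressed on group and the four covariates | 0.753 | not recorded |
| The same four plus baseline, each with its time interaction | -0.002 | not recorded |
| Post-test ANCOVA, four covariates and baseline | -0.002 | 2.21 |

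Over 400 complete data sets the largest difference between the stacked estimates with and without covariates was about 1e-13. The invariance does not depend on the settings; the lap values do. Much of the 2.638 is chance, given a standard error near 2.1.

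With an unchanged estimate, the stacked p-value went from 0.619 to 0.598 to 0.193. Adding baseline brought the standard error close to, and slightly below, the random-intercept value (2.02 against 2.07).

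**Size of what stays in.** If change rises by c laps per unit of x and the groups differ by d in mean x, the unadjusted estimate is off by c x d. The protocol gives neither figure. As an illustration for sex, with c from 0 to 4 laps and d from 0 to 0.30, the bias runs from 0 to 4 x 0.30 = 1.2 laps, or 1.2/6 = 20% of the six-lap target. In a separate simulation of 300 data sets with age-related change and true effect 0, the estimate averaged 1.21 laps with and without age and baseline as main effects, and 0.03 once age x time was added.

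**Limits of exactness.**
- With about 15% of post-tests missing, adding covariates moved the stacked estimate by 1.2 laps on average in absolute value, but the mean over 400 data sets was 0.267 without and 0.266 with them.
- With other links the shift was small or nil for the covariates alone: logit -0.046 to -0.048, gamma-log -0.038 to -0.037, Poisson-log unchanged. Gamma-log with baseline gave -0.058.

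**The case against.** The strongest reply is that the protocol never says main effects. A repeated-measures general linear model, in which between-student covariates act on each timepoint, would regress the time contrast on them and escape the problem. That is a real possibility. It is not the plain reading, though: the section spells out the one interaction it wants and names none for the covariates. If the repeated-measures form was meant, a short clarification settles it.

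Three further points stand and limit the finding.

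- A reader might infer that the planned estimate adjusts for no confounding at all. The documents do not support this. Group x time is a difference in differences, so stable level differences between classes are already removed; only confounding of change remains.
- A reader might infer that adjusted and unadjusted results will be numerically identical in this trial. That needs complete pairs and an identity link. The Sample size calculation section expects 5% attrition and 10–15% data loss, and no link is stated for the psychological outcomes.
- A reader might infer that post-test ANCOVA is simply the correct analysis. In non-randomised groups neither it nor change analysis dominates. With a stable pre-existing group difference and a true effect of 6 laps, change analysis averaged 5.97 and ANCOVA 7.31 in simulation; in another run with true effect 0, ANCOVA averaged 0.66.

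It is also fair that confounding control is not the only stated use of the covariates. The Anthropometry section gives understanding differences by weight status as the purpose. The abstract nevertheless presents the group comparison as accounting for covariates.

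**Conclusion.** The point holds in a bounded form. With covariates as main effects, an identity link and complete pairs, the listed covariates leave the group x time estimate exactly at the raw difference in mean change. With missing post-tests or another link this is approximate; in the missing-data simulation the estimates moved from one data set to the next but their average did not. Confounding of change and regression to the mean are therefore not adjusted, despite the abstract's description and the lack of randomisation.

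The size in this trial cannot be known from the document. It is zero if change is unrelated to the covariates or the groups are balanced on them, and about 1.2 laps against a six-lap target under the illustrative settings above.

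Separately, using the baseline outcome as both outcome row and covariate changes the stacked standard error and p-value without changing the estimate. This should be put right before analysis.

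**What to change.** - In the two-timepoint model, enter each adjustment covariate together with its interaction with time. With complete pairs this is equivalent to regressing change on group and the covariates.
- Remove the baseline outcome from the covariate list of that model.
- Report post-test ANCOVA, with the baseline outcome as a covariate, alongside as a sensitivity analysis, and say that the two rest on different assumptions when groups are not randomised.
- Treat co-design involvement separately. In the HIIT-versus-control model it is nested within HIIT, so its time interaction would turn group x time into HIIT Only against control. In the co-design model it is the group factor itself.

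The cost is a change of wording, a few more model terms and slightly wider standard errors. All covariates are already collected. Students without a pre-test will need a stated rule in the change and ANCOVA analyses.

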### Recruitment and participants

Schools in greater Brisbane will be recruited to *Making a HIIT* through purposeful sampling. Schools with known contacts will be identified and contacted one by one until three schools agree to participate. The aim is to consecutively recruit one co-educational school, one boys’ school, and one girls’ school. The first school will be used as a pilot school to trial the co-design lessons and adapt them if needed before starting in the next two schools. It will include all of the phase one activities and the questionnaires pertaining to students’ motivation, enjoyment, and self-efficacy towards HIIT. The range of included schools aims to help understand potential sex and school-based differences to comprehensively evaluate the integration of co-designing HIIT within HPE.

The head of the HPE department and HPE teachers will be informed of the study and will be involved in class selection for the study. Interested teachers will need to provide informed consent to participate. All students in the classes of consenting teachers will be eligible to participate as *Making a HIIT* will be conducted as part of the curriculum. However, only students who provide parental consent and student assent will have their data collected as part of the study. Students will be excluded if they are unable to participate in the HIIT workouts due to injuries or other reasons. Students will be in either Year 7 or Year 8 (aged 12–14 years) as these 2 years share the same curriculum content descriptions [15]. The flexibility of using Year 7 or 8 allows schools to meaningfully integrate the work conducted as part of the study in their curriculum according to their local needs.

Within each school, *Making a HIIT* will recruit three groups of participants: Group 1) HPE classes involved in the co-design of the HIIT workouts in phase one and who use the HIIT workouts in phase two (Co-Designers); Group 2) HPE classes that use the HIIT workouts in phase two but are not involved in the co-design (HIIT only); and Group 3) HPE classes that continue normal HPE lessons in phase two and are not involved in the co-design (control group). In the pilot school, only one class will be recruited for each group. In the second and third school, two classes will be recruited for each group.

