#### Enjoyment

Enjoyment of general physical activity will be measured for all groups using physical activity enjoyment scale (PACES) before the intervention [61]. The version used in adolescents and youth includes the prompt “When I am active” and 16 phrases that students rank on a 5-point Likert scale from 1 (Disagree a lot) to 5 (Agree a lot) [62]. The overall score is calculated by summing the 16 responses and dividing by the number of questions, with a higher score demonstrating greater enjoyment. It has been validated for both children and adolescents [63]. Enjoyment of general physical activity will be used as a covariate for understanding enjoyment of HIIT specifically.

Enjoyment of HIIT will be also measured using the PACES questionnaire. The stem of the questionnaire will be changed from “When I am active” to “When I am participating in HIIT”. Enjoyment has previously been shown to mediate the effects of school-based physical activity interventions and will be a key variable to examine in this study [64]. The PACES questionnaire on HIIT will be used as an outcome variable examining differences in groups and time.

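### Covariates are to be picked by pairwise tests on the trial's own data, although groups are not randomised and other sections already commit to three of them

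*Protocol article*

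**What the plan says.** The Phase two Data analysis section names the candidates as "Potential covariates, such as sex, age, BMI, involvement in co-design, baseline physical activity levels, baseline physical activity enjoyment, and baseline levels of the dependent variable", and continues that these "will be identified using two-by-two tests and included in the model where appropriate". It gives no threshold. It does not say whether each covariate is tested against group or against outcome. The fitness and executive function models contain group, timepoint and their interaction.

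Three measurement sections speak without any condition:
- Anthropometry: the body-size measures "will be used as covariates in the study to understand differences based on body weight status".
- General physical activity levels: the PAQ-C score, "which will be used as a covariate in data analysis".
- Enjoyment: "Enjoyment of general physical activity will be used as a covariate for understanding enjoyment of HIIT specifically".

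On allocation, the Discussion states: "This study does not include randomisation as it is not feasible in our protocol based on school timetables and preferences for class involvement". Recruitment and participants adds that the head of department and the teachers "will be involved in class selection for the study".

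**The concern.** In a randomised trial, a poor covariate rule mostly costs precision. Here the groups are intact classes, placed according to timetables and preferences, so systematic differences between them are to be expected. The Abstract presents regression on covariates as the way group differences will be handled. Making that adjustment depend on a test has four consequences:

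- A non-significant result is read as no confounding, when it may only reflect limited numbers.
- The set can differ between the shuttle run, the long jump, the two cognitive tasks and each questionnaire, so estimates are not adjusted alike.
- The reported standard error ignores the selection step.
- The baseline outcome is itself a candidate. In a model of change, a pairwise test would then decide between an unadjusted change comparison and a baseline-adjusted one. In non-randomised groups these can estimate different effects.

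An analyst also cannot obey both the conditional rule and the three unconditional commitments if BMI, PAQ-C or PACES fails its test.

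**Working it through.** **No figure to reproduce.** The article gives no rate at which covariates would be dropped. Its 44 students per group is used below only as an input. It does reproduce: with f = 6/22 = 0.273 and three groups, N = 132 gives a critical F of 3.066 and power 0.798, and N = 133 gives power 0.801. Whether that calculation suits the planned contrast is a separate matter.

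**Numbers available** (Sample size calculation; Recruitment and participants). "In the second and third school, two classes will be recruited for each group", so fitness and executive function rest on 2 x 3 x 2 = 12 classes, four per group. The three pilot classes add questionnaires, making 15 for those outcomes. Analysable students per group over four classes:
- low: 4 x 25 x 0.75 x 0.95 x 0.85 = 61
- high: 4 x 30 x 0.80 x 0.95 x 0.90 = 82

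Pooled HIIT v control is therefore 88 v 44 (at the stated 44), 122 v 61 or 164 v 82.

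**Reading A: covariate tested against group.** Assumed: two-sided p < 0.05, student-level test, true imbalance d in SD units.

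P(flag) = P(|Z + d / sqrt(1/n1 + 1/n0)| > 1.96)

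For d = 0.3:
- 88 v 44: 0.3/0.185 = 1.62, flagged 0.37, missed 63%
- 122 v 61: 0.3/0.157 = 1.91, flagged 0.48, missed 52%
- 164 v 82: 0.3/0.135 = 2.22, flagged 0.60, missed 40%

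| True imbalance | 88 v 44 | 122 v 61 | 164 v 82 |
|---|---|---|---|
| 0.2 SD | 81% missed | 75% | 68% |
| 0.3 SD | 63% | 52% | 40% |
| 0.5 SD | 23% | 11% | 4% |

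With p < 0.20 at 88 v 44 the misses are 57%, 36% and 8%. A class-level test (8 v 4 classes, 11 students each, assumed ICC 0.1) misses 0.3 SD 82% of the time and 0.5 SD 59%.

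**Reading B: covariate tested against outcome.** Fisher z with n = 132: P(miss) is approximately P(Z < 1.96 - atanh(r) x sqrt(129)).
- r = 0.1: missed 79%
- r = 0.2: 0.203 x 11.36 = 2.30, missed 37%
- r = 0.3: 0.310 x 11.36 = 3.52, missed 6%
- r = 0.5 or more: about 0%

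**What a miss costs, post-test comparison.** Simulation at 88 v 44, no treatment effect, screening on group imbalance:

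| Imbalance, covariate-outcome r | Never adjusted | Screened | Fixed set |
|---|---|---|---|
| 0.36 SD, 0.5: bias | 0.18 SD | 0.05 SD | 0.00 SD |
| 0.36 SD, 0.5: type I error | 0.15 | 0.05 | 0.05 |
| 0.30 SD, 0.8: bias | 0.24 SD | 0.10 SD | 0.00 SD |
| 0.30 SD, 0.8: type I error | 0.27 | 0.07 | 0.05 |

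Screening on the outcome instead gave bias of about 0.00 SD at r = 0.5 and r = 0.8.

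**What a miss costs, stated group x time model.** With both timepoints complete, a covariate that takes the same value in both rows cancels from the within-student change. Added as a main effect, it leaves the interaction unchanged. In a simulation with imbalance 0.36 SD and a slope of the covariate on change of (0.6 x 0.5 + 0.3) - 0.5 = 0.1, the expected bias is 0.36 x 0.1 = 0.036 SD. The interaction estimate averaged 0.037 without the covariate, 0.037 with it as a main effect (largest difference below 1e-14), and 0.001 with covariate x time. What matters is therefore whether the covariate predicts change, and the form in which it enters.

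**The case against.** The other side has four fair points.

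1. The article fixes neither the threshold nor the type of test, and it leaves room for judgement. A reader might infer from the middle of the first table that real confounders are dropped about half the time. The documents do not support that: the rate runs from about 0% to over 80% according to assumptions that the article does not make, and Reading B keeps strong predictors.
2. A reader might multiply a 0.3 SD imbalance by an assumed slope of 0.4 and the 22-lap SD to get 2.6 laps of bias. That is the bias of a post-only comparison that is never adjusted. It is neither the result of the screen nor the bias of the stated group x time contrast, where a covariate acting equally at both timepoints cancels. It should not be used.
3. Screening on imbalance removes much of the bias, and in most simulated cases type I error stayed near 5%.
4. The three measurement sections may only describe the role of each measure, with the Data analysis section governing.

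The first three limit the size of the harm but do not defend the rule. Exact cancellation needs complete data, while the article expects 5% attrition and 10-15% data loss. The listing of the baseline outcome as a candidate leaves an ANCOVA-type model open. On the fourth, the commitments are worded without condition, so the sections still need to agree. Nor is this a detail left to a fuller document: the article states a selection rule.

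**Conclusion.** The point holds as a fault in the stated covariate rule and as an inconsistency between sections. The inconsistency needs no assumption. The statistical fault rests on two facts in the article: allocation is not randomised, and staff are involved in selecting classes. It does not require that staff alone decide.

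The size is only illustrative. If the screen is covariate-by-group at p < 0.05, a true 0.3 SD imbalance is missed about 40-63% of the time over the plausible numbers. If it is covariate-by-outcome, strong predictors are almost always kept and only weak ones are lost. In the post-only simulations shown, screening on group imbalance left 0.05 to 0.10 SD of bias. In the group x time model, bias equals imbalance times the slope on change, and the article gives no value for that slope. This should be corrected before analysis, but it does not by itself invalidate the design.

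**What to change.** Delete the two-by-two test step. Fix the adjustment set in advance, to be used whatever the baseline comparisons show, and state how each covariate enters.

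- **Fitness and executive function:** ANCOVA of the post-test on group, with pre-test value, school, sex (where school does not determine it), age, BMI and PAQ-C. If the group x time model is kept instead, enter the covariates as covariate x time, and do not also enter the pre-test value, which is already an outcome row. Choose one form now.
- **Co-design outcomes:** school, sex, age, BMI and PAQ-C, plus general PACES for HIIT enjoyment as the Enjoyment section states, restricted to variables not affected by phase one. PAQ-C and PACES are collected just before phase two, after Group 1 has done its co-design lessons, so the plan should say that they are assumed unaffected, or leave them out.
- **Involvement in co-design** is part of the exposure rather than a background characteristic. It belongs in a named contrast, not in the covariate list.
- Align Anthropometry, General physical activity levels, Enjoyment and Data analysis with this set.

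The cost is a few degrees of freedom at student level and a small change in model form. No extra data are needed.
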